## **STUDY OBJECTIVES**

### **Primary objective**

To evaluate the efficacy and safety of early CR after AMI and its effect on physical fitness, morphology, and cardiac function.

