### **Secondary objectives**

- To assess the variation in functional capacity by measuring cardiorespiratory fitness after in-hospital CR, using maximum VO2 (maximum oxygen consumption) as a result measure;
- To analyze the dose of aerobic training provided to patients in in-hospital CR and its impact on the outcome of functional capacity;
- Relate the standard method of measuring VO2, the cardiopulmonary test, to a submaximal evaluation method, the 30s sit-to-stand test, evaluating its validity and reproducibility;
- Observe the influence of early CR on the morphological parameters of ventricular remodeling through nuclear magnetic resonance (NMR);
- Investigate heart rate variability after early cardiac rehabilitation.
- Identify the rate of adverse events and the safety level of the protocol evaluated in this clinical trial;

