## **Sampling and Recruitment**

Participants will be recruited from the adult intensive care unit (ICU) shortly after admission for a percutaneous coronary intervention (PCI) procedure. The sample size was calculated using the OpenEpi software through the mean difference found in a previous study (29) with in-hospital CR for analysis of maximum oxygen consumption (VO2). A number of 7 participants per group was verified with a total of 14 for the sample considering a significance level of 5%, and a statistical power of 80%. Adding a 30% rate for possible losses during the study, we chose to recruit 12 participants per group for a total sample size of 24 patients. The patients included in the study will be patients admitted to the adult ICU at HUOL with a confirmed clinical diagnosis of AMI (ECG and cardiac enzymes) with or without ST elevation and uncomplicated (Killip I or II), undergoing percutaneous coronary intervention (PCI) with success (Timi flow 2 or 3), aged between 18 years and 70 years and of both sexes, classified as low risk (EF>50%, absence of ventricular dysrhythmias, absence of clinical depression and ischemic signs or symptoms after the procedure) according to the American Association of Cardiovascular and Pulmonary Rehabilitation (AACPR) risk classification (50) and ability to provide informed consent. Exclusion criteria determined include the presence of musculoskeletal disorders that prevent the performance of exercises, signs, and symptoms of cardiac ischemia or decompensation, atrial or ventricular arrhythmias, and diagnosed pulmonary diseases (e.g., pulmonary hypertension, COPD, among others).

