## **Statistic Strategy**

The variables of interest will be analyzed using the software (Graph Pad Prism version 7.0) and initially evaluated for the normal distribution of data using the Shapiro-Wilk test considering  $n < 30$ . In the case of data with normal distribution, they will be analyzed for the mean and standard deviation. Data without normal distribution will be analyzed for median and percentiles. Comparison analyses of the physical functional variables of the 30CST, MRI morphological variables, and HRV cardiac functional variables of the PRE-CR and POST-CR times of each group will be performed using the Wilcoxon test if the data were non-parametric and the paired t-test if the data were parametric. Comparison between the control and intervention groups for CPET will be performed using the independent t-test or the Mann-Whitney test, depending on the normality of the data. The reliability and validity of the 30CST will be analyzed using Spearman's correlation and the intra-examiner reliability coefficient. For all hypothesis tests, a significance of 5% probability ( $P < 0.05$ ) of error will be assigned.

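### No primary endpoint is named: the trial is sized on VO2, which is listed as secondary, so the stated 5% error and 80% power do not describe the primary objective

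*Protocol*

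**What the plan says.** The Primary objective reads: "To evaluate the efficacy and safety of early CR after AMI and its effect on physical fitness, morphology, and cardiac function". No variable, time point or comparison is attached to it. The last paragraph of the Introduction gives a different general objective, centred on describing the exercise dose and its effects. Study Design declares a superiority hypothesis, also without naming a variable.

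The first bullet under Secondary objectives measures cardiorespiratory fitness "using maximum VO"2 as its result.

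Sampling and Recruitment takes its effect from an earlier trial "with in-hospital CR for analysis of maximum oxygen consumption", "considering a significance level of 5%, and a statistical power of 80"%. The result is: "A number of 7 participants per group was verified with a total of 14 for the sample". After a 30% allowance for losses, 12 per group (24 in total) are to be recruited.

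The Statistic Strategy plans paired pre-post tests in each group for the sit-to-stand test (30CST), MRI and HRV variables. It plans an independent-groups test for the cardiopulmonary test only. It closes with: "For all hypothesis tests, a significance of 5% probability".

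**The concern.** A superiority trial needs one stated result that decides whether the treatment worked, and its error rate and power should refer to that result. Here the level called primary has no such result, and the outcome that carries the power calculation sits one level down. A reader of the final report could not tell whether a neutral VO2 result with, say, an improved HRV index in the intervention arm counts as success or failure.

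The flat 5% rule does not settle this, because it treats every test alike. With 24 patients and many variables, some significant result is easy to obtain. Most of the planned tests do not compare the arms at all.

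**Working it through.** **1. The plan's own figure.** The 7 per group cannot be reproduced, because no mean difference or SD is given. Working backwards with the normal approximation, n per group = 2(z₁₋α/₂ + z₁₋β)²/d². At d = 1.5 this is 2(1.960 + 0.842)²/2.25 = 15.70/2.25 = 6.98, which rounds up to 7. Seven per group corresponds to d of about 1.50 to 1.61 two-sided, or 1.33 to 1.43 one-sided (sidedness is not stated). For 30% loss, 7/0.7 = 10 per group. The protocol says 12 was chosen, which covers this. All of it concerns VO2 only.

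**2. Counting the tests as the Statistic Strategy plans them.**
- 30CST: 1 variable.
- MRI (Cardiac morphology): end-systolic volume, end-diastolic volume, ejection fraction and scar score, 4 variables.
- HRV (Heart Rate Variability): SDNN, pNN50, HF, LF and LF/HF, 5 variables.
- That is 10 variables, each tested pre-post in 2 arms: 10 × 2 = 20 tests.
- VO2 from the cardiopulmonary test, between arms: 1 test.
- Total 21. No safety test is counted, because the safety section collects adverse events from sessions in the intervention group only.

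**3. Chance of at least one significant result, all nulls true.** Under independence this is 1 − 0.95^k.
- k = 21: 1 − 0.95²¹ = 0.659.
- k = 3 (one test per domain): 1 − 0.95³ = 0.143.

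The variables are plainly correlated. Ejection fraction is computed from the two volumes, and LF/HF from LF and HF. A simulation of the 21 tests took equal correlation within each arm, independent arms and an independent VO2 test:

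| Within-arm correlation | At least one P<0.05 |
|---|---|
| 0.3 | 60% |
| 0.5 | 52% |
| 0.7 | 41% |

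**4. What the 20 paired tests can show.** Suppose both arms recover equally, so that there is no treatment effect. With 12 patients in an arm and a true standardised change of 0.5 (an assumption), a paired t-test is significant with probability 0.353. At 0.8 it is 0.714. The chance that the intervention arm is significant and the control arm is not is 0.353 × 0.647 = 0.228, or 0.714 × 0.286 = 0.204. This is for a single variable.

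**5. Effect of naming one endpoint.** With VO2 as the sole primary endpoint, the error rate for the efficacy conclusion is 5% and the 7 evaluable per group stands. Keeping three co-primary domains with Bonferroni (0.05/3 = 0.0167) at d = 1.5 would need 2(2.394 + 0.842)²/2.25 = 9.3, so 10 evaluable per group. With 30% loss that is 10/0.7 = 14.3, so 15 recruited per group against the planned 12.

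**The case against.** The best defence is that the labels mislead. The contents list calls the two levels general and specific objectives, and the bullets under Secondary objectives simply break the primary statement into parts: VO2 for fitness, MRI for morphology, HRV for cardiac function, adverse events for safety. VO2 lies within physical fitness, the trial is sized on it, and it alone gets a between-arm test. On that reading VO2 is the main outcome in practice. This stands in part: it would be wrong to infer that VO2 was deliberately made subordinate. But the protocol still never names a primary endpoint, and its headings put VO2 in the lower tier.

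Secondly, a reader might infer that any one significant result would be taken as proof of efficacy, and hence that a false-positive headline is likely. The protocol contains no such rule; it sets a per-test threshold. Multiplicity control may also sit in a statistical analysis plan that is not shown, so its absence here is not a fault in itself. Both points stand.

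Thirdly, a reader might count the two MRI follow-ups separately and reach 29 tests and 77%. The Statistic Strategy names only a pre and a post time, and the Appendix A form has space for two MRI results, so that count needs a test the section does not name. Counting one test per outcome (11 or 15 tests; 43% or 54%) matches no planned analysis either, because 30CST, MRI and HRV are not compared between arms.

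Lastly, a significant pre-post change after infarction may be real recovery and not a false positive. This stands, and it is why the percentages above are not a false-efficacy rate.

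**Conclusion.** The point holds as a contradiction within the protocol. The primary objective has no deciding endpoint, the only powered outcome is listed as secondary, and the stated 5% and 80% therefore do not apply to the primary objective as written. An analysis plan could not remove this without changing the objectives.

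The size of the multiplicity problem is conditional. It is about 66% for 21 independent tests, roughly 40% to 60% with correlation, and 14% with one test per domain. Each figure assumes that all nulls are true and that any significant result could carry the claim. The documents do not support saying that a false headline is likely; they support saying that nothing in the protocol prevents one. The 20 within-arm tests add a separate route, since recovery in both arms can make them significant without a treatment effect.

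This should be fixed, but it does not undermine the design: the remedy is wording, and the sizing, test and schedule already fit it.

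**What to change.** - Name peak VO2 at the 30-day reassessment, compared between arms, as the single primary efficacy endpoint, tested at 5%. Use one term throughout, since the protocol alternates between maximum and peak.
- Align the Primary objective, the Secondary objectives, the general objective at the end of the Introduction and the Statistic Strategy with Sampling and Recruitment.
- Make 30CST, MRI and HRV secondary, reported as between-arm differences with 95% confidence intervals. State that neither these nor the within-arm pre-post tests support an efficacy conclusion.
- Keep safety as a separate descriptive objective.

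The cost is a few sentences. The 12 per group is unchanged. The downside is that a favourable MRI, HRV or 30CST result can no longer carry the efficacy claim if VO2 is neutral.

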## **Ethical Aspects**

This study will be submitted to the Ethics and Research Committee of the University Hospital Onofre Lopes, as determined by Resolution nº 466/12 of the National Health Council. In addition, all participants will be guaranteed the provision of a free and informed consent form (Appendix D), the term of institutional authorization for the use of patient documents (Appendix E), and ensured, throughout the study, the maintenance of secrecy and anonymity of participants.

## **RISKS AND BENEFITS**

The risks that the patients involved in the research may present are those inherent to physical activity such as dyspnea, dizziness, fatigue, exhaustion, hypotension, muscle strains, or joint pain. However, the risks will be minimized through the following measures: the proposed exercise will occur within the safety criteria established by the American College of Sports Medicine; For cases of more serious intercurrents such as atrial and ventricular arrhythmias, cardiac decompensation or even cardiorespiratory arrest, the sector has material for cardiorespiratory resuscitation, as well as training of all professionals from the ICU and cardiology ward to manage possible intercurrents.

Regarding the semi-supervised phase, patients will only perform low-intensity exercises with which they will already be adapted during hospitalization, in addition to the large evaluation filter to which they will be submitted to be chosen through the risk stratification of the American Association of Cardiovascular and Pulmonary Rehabilitation (AACPR) (50). Finally, only low-risk patients will be eligible and will undergo semi-supervised follow-up after hospital discharge as recommended by the latest 2020 Brazilian Cardiovascular Rehabilitation Guideline (54).

Among the benefits of this research for the participants, we will have the availability of information about the disease, evaluation, and professional advice on functional capacity and cardiorespiratory fitness, with the supply of an individualized functional exercise prescription booklet after the CPET at the end of the study (Appendix F) with instructions regarding the performance and dose of the exercise, which will lead to a greater stimulus to efficient self-care, enabling better control of your disease, reducing the risk of hospital admissions and morbidity and mortality.

## **RESULTS AND IMPACTS EXPECTED**

It is expected to observe through this research a new model of prescription of aerobic exercise in early cardiac rehabilitation based on the target dose of exercise. In addition, it is expected to verify the magnitude of the clinical impact of carrying out this prescription model through the analysis of cardiorespiratory fitness, measures of submaximal functional capacity through the chair sit-to-stand test, and the morphological and functional parameters of the heart.

This research has an impact on the process of in-hospital cardiac rehabilitation and early follow-up since it outlines a new therapeutic strategy that could make the CR process more efficient in changing the functional capacity of patients and, therefore, in the clinical prognosis of these patients. Finally, it provides a model for calculating the intensity and dose of aerobic exercise, favoring its practical applicability in hospitalization units.

This work may also stimulate new lines of research since the analysis of the ideal aerobic exercise dose within CR still needs to be extensively studied in order to obtain a firm consensus about the therapeutic window to be used with patients with heart disease. It is also expected that this project will present all the results at a national and international level, as well as publish articles in journals with a good impact factor ( $>1$ ), Qualis A1-A2. Finally, it is understood that the study will contribute to greater importance of the application of this type of rehabilitation within Cardiovascular Physiotherapy.

## TIMELINE

| Activity               | Months
(2022) |     |     |     |     |     |     |     |     |     |     |     |
|------------------------|------------------|-----|-----|-----|-----|-----|-----|-----|-----|-----|-----|-----|
|                        | Jan              | Feb | Mar | Apr | May | Jun | Jul | Aug | Sep | Oct | Nov | Dec |
| Literature review      | X                | X   | X   | X   | X   | X   | X   | X   | X   | X   | X   | X   |
| Submission to CEP-HUOL |                  |     |     |     | X   |     |     |     |     |     |     |     |
| Pilot study            |                  |     |     |     |     |     | X   |     |     |     |     |     |
| Data collect           |                  |     |     |     |     |     | X   | X   | X   | X   | X   | X   |
| Project qualification  |                  |     |     |     |     |     |     |     |     |     |     | X   |

| Activity                        | Months
(2023) |     |     |     |     |     |     |     |     |     |     |     |
|---------------------------------|------------------|-----|-----|-----|-----|-----|-----|-----|-----|-----|-----|-----|
|                                 | Jan              | Feb | Mar | Apr | May | Jun | Jul | Aug | Sep | Oct | Nov | Dec |
| Literature review               | X                | X   | X   | X   | X   | X   | X   | X   | X   | X   | X   | X   |
| Discussion of the results found | X                | X   | X   | X   |     |     |     |     |     |     |     |     |
| Article submission              |                  |     |     |     | X   | X   | X   |     |     |     |     |     |
| PhD defense                     |                  |     |     |     |     |     |     | X   |     |     |     |     |

## BUDGET ESTIMATED (formulary according to the local ethical committee)

| Permanent Material                        |            |          |                 |
|--------------------------------------------------|------------|----------|-----------------|
| Item                                             | Unit price | Quantity | Total (R\$)     |
| Treadmil (Centurion 300)                         | 995,00     | 1        | 995,00          |
| Stethoscopy (Littmam)                            | 500,00     | 1        | 500,00          |
| Pulse Oxymeter (Nonin Onyx- 9500)                | 300,00     | 1        | 300,00          |
| Chest strap heart frequency meter (H10 – POLAR)  | 500,00     | 2        | 1.000,00        |
| Notebo"r 14" DELL inspiron 14-2630 preto core i3 | 2.400,00   | 1        | 2.400,00        |
| Subtotal                                  |            |          | 5.195,00 |

| Material de consumo
No-permanent |            |          |               |
|---------------------------------------------|------------|----------|---------------|
| Item                                        | Unit price | Quantity | Total (R\$)   |
| Toner Printer                               | 45,00      | 1        | 90,00         |
| paper A4                                    | 15,00      | 3        | 45,00         |
| Pencil (box)                                | 10,00 1cx  | 1cx      | 10,00         |
| Plastic folder                              | 5,00       | 3        | 15,00         |
| Eletcrodes for ECG (Meditrace)              | 40,00 cx   | 10       | 400,00        |
| Paper envelopes                             | 73,00 cx   | 1        | 73,00         |
| Subtotal                             |            |          | 633,00 |

Resources spent on consumables and permanent materials amount to R\$ 5,828.00. Part of these expenses, referring to permanent materials, are institutional assets and are available for research. The rest of the amount will be entirely the responsibility of the researcher. In addition to permanent and consumable materials, the study will require the use of the sector's telephone (CORE-HUOL) to make calls to patients in the semi-supervised rehabilitation phase and call for reassessment.

# APPENDICES

## APPENDIX A - CLINICAL EVALUATION FORM

**FEDERAL UNIVERSITY OF RIO GRANDE DO NORTE**  
**UNIVERSITY HOSPITAL ONOFRE LOPES**  
**Physiotherapeutic Assessment**

Valuation Date: \_\_\_\_ / \_\_\_\_ / \_\_\_\_

Revaluation: \_\_\_\_ / \_\_\_\_ / \_\_\_\_

### IDENTIFICATION AND SOCIODEMOGRAPHIC

**Name:** \_\_\_\_\_ **Medical Record Number:** \_\_\_\_\_

**Date of birth:** \_\_\_\_ / \_\_\_\_ / \_\_\_\_ **Age:** \_\_\_\_ **Telephone:** \_\_\_\_\_

**Address:** \_\_\_\_\_

**Sex:** ☐ M ☐ F **Weight:** \_\_\_\_ **Height:** \_\_\_\_ **Marital status:** ☐ Married ☐ Single ☐ Divorced ☐ Widower

**Education:** ☐ Illiterate ☐ 1st degree ☐ 2nd degree ☐ 3rd degree ☐ Complete ☐ Incomplete

**Profession:** \_\_\_\_\_

### CLINICAL DATA

**Cardiovascular risk factors:** ☐ SAH ☐ DM ☐ Dyslipidemia ☐ Sedentary ☐ smoker ☐ Family history  
☐ Overweight

**Cardiovascular medication POS AMI:** ☐ Beta blocker  
☐ ACE inhibitors  
☐ Diuretics  
☐ Statins  
☐ Antiplatelet agents  
☐ Hypoglycemic agents  
☐ Others

**STEMI:** ☐ Yes ☐ No **Localization:** ☐ Anterior ☐ Lower ☐ Side

**Angioplasty:** ☐ Stent Culprit artery: \_\_\_\_\_ **Killip:** \_\_\_\_\_ **Timi:** \_\_\_\_\_

**Time to reperfusion:** \_\_\_\_\_ **CPK (peak):** \_\_\_\_\_ **Troponin (peak):** \_\_\_\_\_

**PHYSICAL EXAMINATION PER SESSION**

**Session 1:** Session start: HR:\_\_\_\_\_bpm RF:\_\_\_\_\_bpm SpO2:\_\_\_\_\_ % BP:\_\_\_\_\_mmHg  
End of session: HR:\_\_\_\_\_bpm RF:\_\_\_\_\_bpm SpO2:\_\_\_\_\_ % BP:\_\_\_\_\_mmHg  
Security: ☐ Angina ☐ Arrhythmia \_\_\_\_\_ ☐ Borg>=13 ☐ Fall of SBP>=10mmHg  
☐ CPA ☐ Others:\_\_\_\_\_ Vasoactive drug (Dose) ☐ \_\_\_\_\_ Devices:\_\_\_\_\_  
\_\_CR summary:\_\_\_\_\_

**Session 2:** Session start: HR:\_\_\_\_\_bpm RF:\_\_\_\_\_bpm SpO2:\_\_\_\_\_ % BP:\_\_\_\_\_mmHg  
End of session: HR:\_\_\_\_\_bpm RF:\_\_\_\_\_bpm SpO2:\_\_\_\_\_ % BP:\_\_\_\_\_mmHg  
Security: ☐ Angina ☐ Arrhythmia \_\_\_\_\_ ☐ Borg>=13 ☐ Fall of SBP >=10mmHg  
☐ CPA ☐ Others:\_\_\_\_\_ Vasoactive drug (Dose) ☐ \_\_\_\_\_ Devices:\_\_\_\_\_  
\_\_CR summary:\_\_\_\_\_

**Session 3:** Session start: HR:\_\_\_\_\_bpm RF:\_\_\_\_\_bpm SpO2:\_\_\_\_\_ % BP:\_\_\_\_\_mmHg  
End of session: HR:\_\_\_\_\_bpm RF:\_\_\_\_\_bpm SpO2:\_\_\_\_\_ % BP:\_\_\_\_\_mmHg  
Security: ☐ Angina ☐ Arrhythmia \_\_\_\_\_ ☐ Borg>=13 ☐ Fall of SBP >=10mmHg  
☐ CPA ☐ Others:\_\_\_\_\_ Vasoactive drug (Dose) ☐ \_\_\_\_\_ Devices:\_\_\_\_\_  
\_\_CR summary:\_\_\_\_\_

**Session 4:** Session start: HR:\_\_\_\_\_bpm RF:\_\_\_\_\_bpm SpO2:\_\_\_\_\_ % BP:\_\_\_\_\_mmHg  
End of session: HR:\_\_\_\_\_bpm RF:\_\_\_\_\_bpm SpO2:\_\_\_\_\_ % BP:\_\_\_\_\_mmHg  
Security: ☐ Angina ☐ Arrhythmia \_\_\_\_\_ ☐ Borg>=13 ☐ Fall of SBP >=10mmHg  
☐ CPA ☐ Others:\_\_\_\_\_ Vasoactive drug (Dose) ☐ \_\_\_\_\_ Devices:\_\_\_\_\_  
\_\_CR summary:\_\_\_\_\_

**Session 5:** Session start: HR:\_\_\_\_\_bpm RF:\_\_\_\_\_bpm SpO2:\_\_\_\_\_ % BP:\_\_\_\_\_mmHg  
End of session: HR:\_\_\_\_\_bpm RF:\_\_\_\_\_bpm SpO2:\_\_\_\_\_ % BP:\_\_\_\_\_mmHg  
Security: ☐ Angina ☐ Arrhythmia \_\_\_\_\_ ☐ Borg>=13 ☐ Fall of SBP >=10mmHg  
☐ CPA ☐ Others:\_\_\_\_\_ Vasoactive drug (Dose) ☐ \_\_\_\_\_ Devices:\_\_\_\_\_  
\_\_CR summary:\_\_\_\_\_

**Session 6:** Session start: HR:\_\_\_\_\_bpm RF:\_\_\_\_\_bpm SpO2:\_\_\_\_\_ % BP:\_\_\_\_\_mmHg  
End of session: HR:\_\_\_\_\_bpm RF:\_\_\_\_\_bpm SpO2:\_\_\_\_\_ % BP:\_\_\_\_\_mmHg  
Security: ☐ Angina ☐ Arrhythmia \_\_\_\_\_ ☐ Borg>=13 ☐ Fall of SBP >=10mmHg  
☐ CPA ☐ Others:\_\_\_\_\_ Vasoactive drug (Dose) ☐ \_\_\_\_\_ Devices:\_\_\_\_\_  
\_\_CR summary:\_\_\_\_\_

**Session 7:** Session start: HR:\_\_\_\_\_bpm RF:\_\_\_\_\_bpm SpO2:\_\_\_\_\_ % BP:\_\_\_\_\_mmHg  
End of session: HR:\_\_\_\_\_bpm RF:\_\_\_\_\_bpm SpO2:\_\_\_\_\_ % BP:\_\_\_\_\_mmHg  
Security: ☐ Angina ☐ Arrhythmia \_\_\_\_\_ ☐ Borg>=13 ☐ Fall of SBP >=10mmHg  
☐ CPA ☐ Others:\_\_\_\_\_ Vasoactive drug (Dose) ☐ \_\_\_\_\_ Devices:\_\_\_\_\_  
\_\_CR summary:\_\_\_\_\_

**Session 8:** Session start: HR:\_\_\_\_\_bpm RF:\_\_\_\_\_bpm SpO2:\_\_\_\_\_ % BP:\_\_\_\_\_mmHg  
End of session: HR:\_\_\_\_\_bpm RF:\_\_\_\_\_bpm SpO2:\_\_\_\_\_ % BP:\_\_\_\_\_mmHg  
Security: ☐ Angina ☐ Arrhythmia \_\_\_\_\_ ☐ Borg>=13 ☐ Fall of SBP >=10mmHg  
☐ CPA ☐ Others:\_\_\_\_\_ Vasoactive drug (Dose) ☐ \_\_\_\_\_ Devices:\_\_\_\_\_  
\_\_CR summary:\_\_\_\_\_

**Surplus sessions:** Any adverse events? Which? \_\_\_\_\_

| COMPLEMENTARY EXAMS                                                                                                                                                                                                                                              |                          |
|------------------------------------------------------------------------------------------------------------------------------------------------------------------------------------------------------------------------------------------------------------------|--------------------------|
| Electrocardiogram (1): _____
 Regular rhythm  Atrial fibrillation  Pacemaker  RBBB  LBBB  Others _____ | Date: ____ / ____ / ____ |
| Echocardiogram (1): EF _____ PAP _____ Others: _____                                                                                                                                                                                                      | Date: ____ / ____ / ____ |
| X-RAY (1): _____                                                                                                                                                                                                                                          | Date: ____ / ____ / ____ |
| Cardiac catheterization (1): _____
_____                                                                                                                                                                                                               | Date: ____ / ____ / ____ |
| Cardiac resonance (1): _____                                                                                                                                                                                                                              | Date: ____ / ____ / ____ |
| Cardiac resonance (2): _____                                                                                                                                                                                                                              | Date: ____ / ____ / ____ |
| Heart rate variability (1): _____                                                                                                                                                                                                                         | Date: ____ / ____ / ____ |
| Heart rate variability (2): _____                                                                                                                                                                                                                         | Date: ____ / ____ / ____ |

| PHYSICAL TESTS                                                                                                                                                                                                                       |                          |
|--------------------------------------------------------------------------------------------------------------------------------------------------------------------------------------------------------------------------------------|--------------------------|
| 30CST (1): Result: _____ Adverse event: _____
Before the test: HR: ____ bpm RF: ____ bpm SpO 2 : ____ % BP: ____ mmHg
End of test: HR: ____ bpm RF: ____ bpm SpO 2 : ____ % BP: ____ mmHg         | Date: ____ / ____ / ____ |
| 30CST (1 + 30min): Result: _____ Adverse event: _____
Before the test: HR: ____ bpm RF: ____ bpm SpO 2 : ____ % BP: ____ mmHg
End of test: HR: ____ bpm RF: ____ bpm SpO 2 : ____ % BP: ____ mmHg |                          |
| 30CST (2): Result: _____ Adverse event: _____
Before the test: HR: ____ bpm RF: ____ bpm SpO 2 : ____ % BP: ____ mmHg
End of test: HR: ____ bpm RF: ____ bpm SpO 2 : ____ % BP: ____ mmHg         | Date: ____ / ____ / ____ |
| 30CST (2 + 30min): Result: _____ Adverse event: _____
Before the test: HR: ____ bpm RF: ____ bpm SpO 2 : ____ % BP: ____ mmHg
End of test: HR: ____ bpm RF: ____ bpm SpO 2 : ____ % BP: ____ mmHg |                          |
| CPET (2): VO 2 Peak: ____ Test time: _____
Derived variables: _____                                                                                                                                             | Date: ____ / ____ / ____ |

